#### **10.4.3 Serious Fall Injuries**

Clinical fractures are defined as fractures involving any skeletal site (except

vertebral) that occur after randomization, are diagnosed because of fracture-related symptoms, are reported to the investigators, and are documented by a definite radiologic diagnosis (radiographs, bone scan, etc.). These fractures are ascertained using a protocol that was originally developed by the FIT (Fracture Intervention Trial) investigators and is now being used in the Osteoporotic Fractures in Men Study.

Data are collected on all hospital admissions. These data are reviewed by an expert physician, who is masked to the intervention group, and who identifies hospital admissions that are primarily attributable to a fall injury, including: fractures, head injuries resulting in loss of consciousness, joint dislocations and other serious joint injuries, severe lacerations, serious internal injuries (e.g., retroperitoneal hematoma) and the major sequelae of aging (rhabdomyolysis, dehydration, and hypothermia).

#### **10.4.4 Pulmonary and cardiovascular outcome adjudication**

All hospital records will be reviewed to determine whether there was a pulmonary or cardiovascular outcome for the following conditions:

**a) Pulmonary outcomes** to be assessed include hospital admission for exacerbation of airway disease (asthma, bronchitis, emphysema, &/or COPD) or pneumonia. Initial ascertainment of pulmonary hospitalizations will be made at the every 6 month follow-up interviews. Medical records will be obtained and reviewed blinded to group assignment. Details of the review and adjudication are provided below.

**b) Cardiovascular outcomes** to be assessed as tertiary outcomes include the combined outcome of:

- Myocardial infarction (MI),
- Angina requiring hospitalization,
- Any stroke (ischemic or hemorrhagic),
- Transitory ischemic attack (TIA) requiring hospitalization,
- Hospitalization for carotid artery disease,
- Hospitalization for congestive heart failure (CHF),
- Hospitalization for peripheral artery disease (PAD) or outpatient revascularization for PAD,
- Ruptured abdominal aortic aneurism (AAA), and
- CVD death.

Initial ascertainment of hospitalizations will be made at the every 6 month follow-up interviews. Medical records will be obtained and abstracted for codes and diagnoses compatible with one of these events and will be blinded to group assignment. This summary data along with a de-identified copy of the records will be forwarded to the DMAQC for review by a central adjudication committee. The committee will be composed of clinicians with expertise in the diagnosis of these conditions (cardiologists, pulmonologists and geriatricians) who will assign presence or absence of each diagnosis using standardized criteria.

If death is reported to be in the hospital or subsequent to a hospitalization (in nursing home, hospice or home), hospital records, autopsy reports if available, and death certificate will be requested and reviewed. Abstraction forms and de-identified records will be forwarded to the DMAQC for review and adjudication by the central adjudication committee based on standard criteria to determine whether one of the cardiovascular outcomes of interest is the underlying cause of death. For out-of-hospital deaths, an interview will be conducted with the previously designated informant to determine the

circumstance of death.

#### **10.5. Ancillary Studies**

Proposals of ancillary studies are subject to review by the Emerging Science Committee.

#### **10.6. Tracking Health Care Utilization and Vital Status, and HIPAA Compliance**

Health care utilization is assessed at baseline and every 6 months using a self-administered questionnaire developed at the University of California San Diego. The measure consists of 12 questions that ask about the frequency of various types of health care utilization over the previous 6 months. The questions ask about utilization of hospital days, emergency care, urgent care, primary care, telephone calls, prescriptions, and medical equipment. Health care costs are calculated by multiplying the frequency of each service by the prevailing community charge. The measure has been validated in a clinical trial of patients with chronic obstructive pulmonary disease.

In compliance with the **HIPAA** and the DHHS' Standards for Privacy of Individually Identifiable Health Information, LIFE accesses personal health information and **medical records** only after obtaining **informed consent**. Social security number, Medicare number, date of birth, and health insurance information is collected. A proxy respondent and two contact persons are also identified.

**Abstraction of hospital records.** Participants are asked to notify study personnel about any hospitalization or serious illness. At each clinic visit or telephone contact, participants are questioned about interim hospitalizations. Since any hospitalization may potentially result in changes in activity level or performance, LIFE abstracts minimal information on all hospitalizations (discharge diagnoses, procedures, and length of stay). Hospitalizations are reviewed to assess study outcomes. For fractures, type of fracture and treatment are verified by review of the medical record. Reports of **death** through regular surveillance or via databases searches are tracked by collecting death certificates and relevant medical records, including autopsy reports if available. For all medical record reviews, standard forms are completed by trained abstractors.

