### 7.3. Successful Aging Program Intervention

#### 7.3.1. Contact Mode and Frequency

The successful aging program arm meets in small groups (approximately 25 participants per group), one time each week for the first 26 weeks of the intervention. From week 27 on, successful aging groups will be offered two times per month with required participation at least once per month. Telephone calls are made after missed visits to problem-solve barriers to attendance and to encourage regular participation. As undertaken in LIFE-P, those participants randomized into the Successful Aging Program will receive an individual 45 minute face to face introductory session, by a health educator, during which time the program is described and questions are answered.

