Expected serious adverse events related to the exercise intervention include in rare instances, heart attack, stroke, and death. Cardiovascular events are assessed using standard protocol measures including ECGs. When a cardiovascular event has occurred, a study physician decides whether it is permissible for the participant to continue interventions. If the LIFE interventions are discontinued for safety reasons, they may be resumed after consultation with the participant's primary care physician.

Serious fall injuries and fractures are assessed using standard protocol measures, including radiographs and hospital records. When a serious fall injury or fracture occurs, a study physician decides whether it is permissible for the participant to continue interventions. If the LIFE interventions are discontinued for safety reasons, they may be resumed after consultation with the participant's primary care physician.

In the LIFE safety monitoring system, participants who report adverse events to any staff person at any time are referred to unmasked medical staff responsible for identifying, recording, and managing these events. Safety-related events are reported in a timely fashion as required by the Data and Safety Monitoring Board and the IRBs responsible for the study. Interventionists and other staff reporting or managing adverse events for safety purposes do not at any time communicate information regarding these events to study assessment personnel.

LIFE maintains an event outcome database that is completely separate and distinct from the safety monitoring system for the intervention group. This is necessary because many of the LIFE staff members are not masked to intervention assignment, and it is critical that the identification and reporting of serious adverse events for safety reasons not bias the study's collection of outcome data. Thus, for outcome purposes, all LIFE participants are systematically queried at clinic visits or on clinic phone calls scheduled according to the protocol to capture outcome data on study outcomes, medical events, or adverse experiences. This separate outcome database contains solely those adverse events that are reported through these regularly scheduled event interviews conducted by designated outcome assessment staff who are masked to intervention assignment.

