All deaths shall be reported within 48 hours to both DSMB and NIA. All Serious Adverse Events shall be reported in a summary format by the blinded treatment arm (A and B) to the DSMB and NIA monthly.

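### Section 10.6 sends hospitalizations reported to unspecified study personnel into outcome review, against section 8.5's masked-interview-only rule, so serious fall injuries above all can be found more completely in the physical activity arm

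*Protocol*

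**What the plan says.** Section 8.5 sets up two streams. In the safety stream, "participants who report adverse events to any staff person at any time are referred to unmasked medical staff". In the outcome stream, the database "contains solely those adverse events that are reported through these regularly scheduled event interviews", and masked assessors conduct those interviews. The stated reason is that many staff know the assignment and "it is critical that the identification and reporting of serious adverse events for safety reasons not bias the study's collection of outcome data". The section also bars staff who handle events for safety from passing them to assessors.

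Section 10.6 describes how hospital records are found. "Participants are asked to notify study personnel about any hospitalization or serious illness". Participants are also questioned at clinic visits and telephone contacts, minimal information is abstracted on every hospitalization, and hospitalizations are then reviewed for study outcomes. Nothing restricts who receives the report, when, or whether that person is masked.

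Section 10.4.3, on serious fall injuries, says "Data are collected on all hospital admissions"; a masked physician then picks out those due mainly to a fall. It names no source for the admissions. Section 10.4.4 opens by putting every hospital record under review for cardiovascular and pulmonary outcomes. It then places initial ascertainment at the six-monthly interviews, as 10.3.6 (g) and (h) also do.

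Contact differs by arm. PA participants are offered two center sessions a week to the end of the trial (Table 7.2.1, section 7.2.5). SA participants meet weekly for 26 weeks, after which section 7.3.1 says: "From week 27 on, successful aging groups will be offered two times per month with required participation at least once per month".

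**The concern.** Field staff cannot apply both rules. If an admission becomes known only because a participant mentioned it at an exercise class, 8.5 keeps it out of the outcome data and 10.6 puts it into outcome review. Under 10.6, the chance that an admission is found depends on how often the participant meets staff, and that depends on the arm. Masked record review does not repair this, because it never sees an SA admission that nobody reported.

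The foreseeable direction is fuller detection in PA, which would hide a benefit or imitate harm. Serious fall injury is most exposed. It is a secondary outcome, its section has no ascertainment rule of its own, and section 12.2 expects so few events that it drops stratification by field center. A handful of extra detections in one arm could therefore move the estimate.

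**Working it through.** **1. The rules side by side**

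| Section | Who takes the report | When | Enters outcome review? |
|---|---|---|---|
| 8.5, outcome database | Masked assessors | Scheduled visits and calls | Yes, and nothing else does |
| 8.5, safety system | Any staff, then unmasked medical staff | Any time | No |
| 10.6 | Study personnel, not specified | Not limited for notification; clinic visits and telephone contacts for questioning | Yes |
| 10.4.3, falls | Not stated | Not stated | Yes, all admissions |
| 10.4.4, cardiovascular and pulmonary | Not stated | Six-monthly interviews for initial ascertainment, but all records in the opening line | Yes |

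The first and third rows conflict. The fourth does not settle the matter. The fifth does so only in part.

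**2. Planned group contacts over the average 2.7 years (section 3.1)**

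- PA: 2 × 52 × 2.7 = 280.8, about 281.
- SA: 26 weekly sessions, then 2.7 × 12 − 6 = 26.4 months.
  - One session per month (the required minimum): 26 + 26.4 = 52.4.
  - Two per month (all offered): 26 + 52.8 = 78.8.
- Ratio: 280.8 / 78.8 = 3.6 to 280.8 / 52.4 = 5.4.

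These are sessions offered, not attended. The ratio shows direction only. It is not a ratio of detection, since one contact is enough to report an admission.

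**3. Effect on the hazard ratio**

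Let s be the share of admissions caught at the scheduled interviews, equal in both arms, and q the share of missed ones recovered through other contacts. Detection in an arm is s + (1 − s)q, and the observed hazard ratio (PA against SA) is the true one times detection in PA divided by detection in SA. The documents give neither s nor q. Assume q = 0.80 in PA and 0.30 in SA.

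| s | PA | SA | Inflation factor |
|---|---|---|---|
| 0.85 | 0.970 | 0.895 | 1.08 |
| 0.90 | 0.980 | 0.930 | 1.05 |
| 0.95 | 0.990 | 0.965 | 1.03 |
| 1.00 | 1.000 | 1.000 | 1.00 |

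At s = 0.85 to 0.95, a true hazard ratio of 0.80 would read 0.80 × 1.026 = 0.82 to 0.80 × 1.084 = 0.87. With weaker recovery (q = 0.50 and 0.20) the factors are 1.05, 1.03 and 1.02. With equal recovery in both arms there is no inflation.

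**4. What such factors do to power (scale only)**

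Section 3.3 states 51% power for cardiovascular events at a hazard ratio of 0.70 and 4% per year. With 1,600 participants split 1:1, exponential event times, 8% per year loss and follow-up uniform over 23-42 months, I get 128 events. Power is then Φ(√(128/4) × |ln 0.70| − 1.96) = 52.3%, within 2 points of the plan.

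If SA detection is 95% of PA detection, the hazard ratio reads 0.70 / 0.95 = 0.74 and power falls to 40%. At 98% it reads 0.71 with power 47%. At 90% it reads 0.78 with power 28%. This shows sensitivity to unequal detection and is not a forecast for cardiovascular events, whose exposure is the less clear one.

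**The case against.** The strongest reply is that 10.6 can be read in line with 8.5. Its questioning at clinic visits and telephone contacts resembles 8.5's scheduled visits and calls, and the protocol generally uses clinic visits for the six-monthly assessments and center-based sessions for the intervention. On that reading only the notification sentence is open-ended, and 8.5's exclusive rule and its bar on passing event information to assessors would govern it. This has force, but 10.6 goes straight on to abstract all hospitalizations and review them for outcomes without pointing back to 8.5, and 10.4.3 does not close the gap.

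Second, both arms are asked at every six-monthly visit, complete a self-administered utilization questionnaire covering hospital days (section 6.2.14), and have proxies interviewed when needed. Only admissions missed by all of these can differ. SA staff also call after a single missed session in the first 26 weeks (Table 7.2.2), whereas PA staff in the adoption phase call after two consecutive unannounced absences (section 7.2.4). These points stand. They limit the size and make the bias a risk, not a finding.

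Third, counting only interview-elicited admissions discards documented events from outcomes with limited power. That is a real cost, which the sensitivity analysis below is meant to cover.

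**Conclusion.** The contradiction between 8.5 and 10.6 is real, and 10.4.3 leaves it open for a secondary outcome. The unequal contact schedule makes fuller detection in PA the likely direction. The inflation factor of about 1.03 to 1.08 rests on assumed interview sensitivity (85-95%) and assumed recovery (80% in PA, 30% in SA), and it vanishes if interviews miss nothing.

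A reader might infer more than the documents support:

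- That 10.6 admits reports made to any staff at any time. That wording is 8.5's, for the safety system; 10.6 simply sets no limit.
- That outcomes are in fact found more completely in PA. The documents show an open route and do not give the share of admissions missed.
- That cardiovascular and pulmonary events are equally exposed. Sections 10.3.6 and 10.4.4 already name the six-monthly interviews; only the opening of 10.4.4 sits badly with that.
- That the factor could reach 1.00 / 0.85 = 1.18. This requires PA to recover every missed admission and SA none, although SA participants also meet staff and receive calls.
- That the monthly serious adverse event summary by arm is wrong. Safety reporting is meant to be inclusive, and nothing in the protocol contradicts it.

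**What to change.** Reconcile 10.6, 10.4.3 and the opening of 10.4.4 with 8.5:

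- State that, for hospitalization-based outcomes, the main between-arm analysis counts an admission only if it was elicited at the scheduled masked interview (participant or proxy) or through an arm-independent source such as the death review.
- Record the source of first report for every admission.
- Keep admissions known only from other reports in the safety system, and add them in a sensitivity analysis.
- In the data and safety monitoring board tables, keep all serious adverse events by arm and add the source of first report as a descriptive column. Do not replace the all-event comparison.

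The cost is wording in three places, one data field, one extra analysis and one table column. The downside is that true admissions never mentioned at a scheduled interview leave the main analysis. Under the assumptions above these are 0.99 − 0.95 = 4 to 0.97 − 0.85 = 12 percentage points of PA admissions, and 0.965 − 0.95 = 1.5 to 0.895 − 0.85 = 4.5 points of SA admissions. They remain in the safety system and in the sensitivity analysis.

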## **11. Data Management and Quality Control**

### **11.1. Data Management**

#### **11.1.1. Field Centers-Screening, Randomization, and Follow-Up Visits**

An internet-based, web browser application is used to manage screening, randomization and follow-up visits in this project. Field Centers access the study web site and initiate the interactive randomization page. Entry into this area is password protected and encrypted. Once security requirements have been satisfied, a series of questions establish identifying and eligibility information, and a participant identification number is issued. When the randomization session is complete, an e-mail process is initiated and a record of the transaction is sent to the clinic coordinator and the project manager at the DMAQC indicating that the participant has been properly appended to the database.

The 'Participant Tracking System' (PTS) is a fully integrated tracking and notification system that advises clinic staff about participant follow-up windows and projects clinic and laboratory workload. Participant tracking begins at screening and randomization and continues automatically throughout the project by integrating participant follow-up data with predetermined follow-up "windows." Reports about protocol deviations are automatically generated and transmitted to the clinic via e-mail attachments. These data are available in the study web site.

A Participant Label tool will also be included in the system, to assist in the creation and printing of the various labels needed during data collection. This system will support multiple label formats and label paper stock.

#### **11.1.2. Data Entry, Verification and Quality Control**

Field Center data coordinators review each set of completed forms for accuracy and completeness. During data entry, key variables are checked for accuracy with the assigned range checks. A review is required for any data entered outside of preset ranges. Override capabilities exist; however these are flagged for review upon receipt by the DMAQC. Through communication with the clinic coordinators, the DMAQC project manager reconciles any responses that continue to be questionable within 30 days. A random verification pass is performed to detect error patterns and logic flaws

#### **11.1.3. Intentionally Blank**

#### **11.1.4. Database Closure**

Upon study completion, after all clinic and laboratory data have been collected and filtered through the appropriate quality control procedures, the database is certified. The database is taken off-line and archived. The final datasets are certified and issued version numbers to synchronize analytic efforts, after which they are distributed in accordance with Steering Committee and Institute policy.

### **11.2. Management of Administrative Data**

**A Web-based administrative tracking and monitoring system** facilitates the flow of information and increases the level of communication within LIFE. Its Web site includes the Study Directory, meeting times and locations, minutes, data reports, IRB status of projects, and other procedural, technical or administrative documents.

### **11.3. Quality Control (QC)**

QC is a shared responsibility of all investigators. The DMAQC takes a vigorous lead in assuring the quality of study databases. The quality and eventual acceptance of all studies depend on issues such as: maintaining randomization integrity, accurately assessing participant eligibility, recording dropouts and adherence, measuring outcome

variables without bias, preventing premature release of results, monitoring and assessing protocol adherence, and avoiding biases in the analysis of the results. QC procedures are devised to monitor screening, data collection, follow-up, clinical measurements, collection of forms, data entry procedures, implementation of interventions and overall scientific and leadership operations.

## 12. Statistical Considerations

### 12.1. Introduction and Aims

The **primary aim** of the LIFE randomized controlled clinical trial is to assess the long-term relative effect of randomization to a physical activity intervention on the **primary outcome** of time until major mobility disability defined as inability to walk 400 m in sedentary persons aged 70-90 years.

The **secondary aims** of the LIFE trial are to assess the relative effect of randomization to the intervention on the following **secondary outcomes**:

- Cognitive function based on the Digit Symbol Test (DSST) and the Hopkins Verbal Learning Test (HVLT)
- Serious fall injuries;
- Persistent mobility disability and the combined outcome of major mobility disability or death;
- Proportion of 400 m walk failures over time;
- Disability in activities of daily living; and
- Cost-effectiveness.

**Tertiary aims** of the LIFE trial are **to explore** the effects of random assignment to the intervention on the following **tertiary outcomes**:

- Mild cognitive impairment / dementia;
- A composite measure of the cognitive assessment battery; and
- The Short Physical Performance Battery (SPPB) score and the 400 m walk speed within ethnicity/race, gender and baseline physical performance subgroups;
- Sleep-wake disturbances;
- Dyspnea and ventilatory capacity;
- Hospital admission or death for exacerbation of airway disease (asthma, bronchitis, emphysema, &/or COPD) or pneumonia;
- Combined cardiovascular events including:
  - Myocardial infarction (MI),
  - Angina requiring hospitalization,
  - Any stroke (ischemic or hemorrhagic),
  - Transitory ischemic attack (TIA) requiring hospitalization,
  - Hospitalization for carotid artery disease,
  - Hospitalization for congestive heart failure (CHF),
  - Hospitalization for peripheral artery disease (PAD) or outpatient revascularization for PAD,
  - Ruptured abdominal aortic aneurism (AAA), and
  - CVD death;
- In addition, as additional **tertiary aim**, we will explore the effect of the length of the intervention on the SPPB score and 400 m walk speed endpoints (i.e. time since randomization by intervention effect).

